**3. Study Procedures**

Female defendants are recruited for this study from two primary types of community-based criminal justice settings: Community Courts and Probation Reporting Sites. By the time they are referred to a community court (e.g. MCC or BCS), female defendants have pleaded guilty to a misdemeanor offense, and have accepted an alternative sanction in lieu of a jail sentence.

At NYC Probation reporting sites, women offenders have been convicted of a misdemeanor or felony offense, and are being supervised while in the community by the NYC Department of probation. Female clients at community courts and probation sites are recruited by research staff via study flyers. Interested potential participants undergo a written informed consent and complete a 10-15 minute screening in a private room, which consists of questions about sexual behaviors, history of drug use, and demographic information (see screening form). If a private room is not available, or if the participant wishes to be screened at a later time, the participant is screened via phone by a dedicated 1-800 number associated with this study. At the time of the screening interview, participants are asked to sign a HIPAA form. Participants are compensated $5 for completing the screening interview. Women who meet eligibility criteria are asked to participate in the study, and told that their decision regarding whether or not to participate in the study does not affect their status with court or criminal justice system. Participants undergo an additional informed consent process, and scheduled to complete a pre-intervention (or baseline) assessment at the SIG Community Research Site.

When a participant arrives for their pre-intervention assessment, they undergo a shortened version of the screener to confirm eligibility. If a woman no longer meets eligibility criteria, she is compensated $10 and will no longer participate in the study. Women who meet eligibility criteria undergo a pre-intervention assessment. The pre-intervention assessment is conducted in a private room and lasts approximately 60 minutes, consisting of demographic information, drug and alcohol use, sexual behaviors, intimate partner violence, measures of depression and PTSD, to be completed on ACASI. Biological assessment for STIs at the baseline assessment involves providing pre-test counseling, asking female participants to provide a vaginal swab (self administered by the participant) which is used to test for gonorrhea, Chlamydia and trichomoniasis, and then providing follow up post-test counseling to notify participants of their results and treatment referrals as needed. Additionally, at baseline assessment, all participants are asked to provide an oral swab to conduct testing for HIV infection, using the OraQuick ADVANCE 15-min oral fluid assay ("rapid test"). We have been approved for Hazardous Materials and currently have a Data Use Agreement with Emory University in Atlanta, GA. (please see attachment) to process the samples collected. Emory University has conducted a number of STI testing protocols for research studies.

**Pre- and Post-test Counseling for HIV/STI Testing:** All participants receive pre-and post-test counseling for HIV and STI testing as mandated by New York State law. Prior to being asked to provide an oral specimen, using the OraQuick test procedures to confirm their HIV serostatus, all participants will receive standard HIV pre-test counseling from the Clinical Research Coordinator (CRC) who be trained and supervised in the conduct of such counseling. Because all study participants receive pre- and post-HIV/STI test counseling, all participants (regardless of condition) are exposed to HIV risk reduction information including sex risk reduction, which helps participants avoid becoming infected with HIV or STIs. Thus, participants in all conditions receive higher quality pre/post HIV/STI test counseling than is the general standard of care outside the study protocol. These procedures are being used in our current studies and are in compliance with the most up-to-date New York State and New York City laws and standards.

**Biospecimen Collection and Testing Procedures for HIV:** After completing baseline measures and the 12 month follow-up, we ask all participants to provide an oral specimen, using the OraQuick test procedures to confirm their HIV serostatus. Sensitivity and specificity for the OraQuick oral fluid assay are 99.3% and 99.8% respectively. Results are available from the rapid test in 15 minutes. If the first OraQuick ADVANCE assay is non-reactive, then no further testing is conducted. If the rapid test is reactive, the participant is informed about the results and a confirmatory OraQuick test is conducted immediately. Regardless of whether the confirmatory rapid test is reactive or non-reactive, participants are informed of the confirmatory results and referred for further confirmatory HIV testing and, if needed, treatment and care. All participants receive standard pre- and post-test HIV counseling from the Clinical Research Coordinator (CRC), who is certified to conduct such counseling. Participants who are identified as HIV seropositive are informed in private and referred to clinical sites for further diagnostic evaluation and care. The CRC notifies the local health department as per legal obligations for HIV reporting.

**Biospecimen Collection, Shipping and Testing Procedures for STIs:** To complement self-reports and provide a more objective outcome, we use biological assays for gonorrhea, Chlamydia, and trichomonas. These STIs are selected based on their high prevalence and incidence in this population, the availability of accurate tests, and because each can be definitively treated with a single oral dose of antimicrobial medication. We assess STIs with DNA amplification assays on self-collected vaginal swab specimens from the women, which have several advantages including stability for transport and ease of collection. Each participant will be asked to obtain one vaginal specimen by inserting a sterile Dacron-tipped swab about 2.5 inches or as far as comfortable into the vagina, rotating it for 15 to 30 seconds, and removing it. The vaginal swabs are placed into separate specimen transport packaging. Refrigerators are utilized for storing specimens between shipment dates. Specimens are shipped within 72 hours of collection. All specimens are shipped and processed by Emory University in Atlanta, GA, using standard handling procedures in specially designed biohazard containers suitable for Dangerous Goods Shipping according to International Air Transport Association (IATA) guidelines. Emory University has worked on other NIH funded studies involving STI testing.

**Notification to Participants of HIV/STI Results and Legal HIV/STI Reporting and Tracing Requirements:** HIV rapid test results are available within 15 minutes and STI test results are available 1 week after a participant provides a specimen for analysis. Participants are informed of the results of the HIV test immediately and STI tests when they arrive at their randomization appointment. Participants who test positive for any of the STIs or HIV are informed privately by the CRC, counseled, and referred for treatment (see treatment protocol below). To reduce this distress, the CRC provides supportive counseling, treatment and referral, as needed. During the informed consent process, we apprise participants that we report positive Chlamydia, gonorrhea, or HIV tests to the New York City Department of Health (NYCDOH), and that this is the same procedure followed when people are tested in a private physician’s office. We explain all procedures in the consent form, up front, including potential risks and benefits (especially the benefit of detecting and getting treatment for an STI and HIV, when symptoms are not observable).

If a participant tests positive for gonorrhea, Chlamydia, or HIV, the CRC completes a Confidential Morbidity Report. The Confidential Morbidity Report, which identifies the STI-positive individual and the specific STI diagnosis, must be received by the NYCDOH within two weeks of the CRC receiving the participant's STI results. Upon the receipt of the Confidential Morbidity Report, NYCDOH initiates contact tracing as per standard procedures. Upon referral, NYCDOH protocol requires that diagnosed individuals be interviewed by a trained Disease Investigation Specialist and asked about their sexual contacts for contact tracing. NYCDOH asks infected individuals whether they would like to disclose positive tests to their partner(s) and bring the partner in for treatment, or whether they would prefer that DOH staff contact the partner. Individuals testing positive for STIs, including HIV, however, are not mandated to, nor can they be coerced to, disclose the names of their sexual partners. Both scenarios offer opportunities for the participant to choose whether or not to disclose with or without support.

**Protocol for STI Treatment:** All participants who test positive for gonorrhea, Chlamydia and trichomoniasis are referred for treatment with a single dose antibiotic therapy that will be administered by licensed physicians who are participating providers for SIG’s current studies, or if the participant prefers, by her primary care provider. All SIG providers accept Medicaid and all other types of insurance. All SIG providers have received human subjects training and NIH certification. If a participant is uninsured and cannot afford treatment, SIG pays for treatment out of in-kind funds. Few participants who test positive for an STI will not have Medicaid or other insurance. The participants STI and HIV serostatus is kept strictly confidential and known only to the participant, the CRC, and the physician who is treating them. These procedures are in compliance with the most up-to-date New York State and New York City laws and standards. Of critical importance is the confirmation of participant’s treatment. From both ethical and methodological reasons, it is imperative that treatment be completed promptly. Thus, the CRC works closely with the participant to confirm that STI treatment has been received. After notification, the participant is treated immediately or scheduled to return to a designated clinical site for treatment by a project clinician. For both ethical and methodological reasons, it is imperative that treatment be completed promptly and confirmation of intervention is obtained. Participants are treated with directly observable state-of-the-art single-dose oral therapy to minimize potential non-adherence to multi-dose medication regimens.

Receiving a positive test result for HIV may produce psychological stress. Study staff/interviewers are trained to provide prevention counseling and provide referrals for HIV care. Although we offer this HIV testing at no cost to the participant, she may choose not to get tested and still be able to participate in the study (i.e. willingness to take the HIV test is not an eligibility criterion).

For participating in the pre-intervention assessment and HIV/STI tests, participants are compensated $35. For the 12 month follow-up assessment and HIV/STI tests, participants are compensated $65. Participants are informed that they can withdraw from the study at any time, and this will also not affect their court or criminal justice status. Participants are instructed how to withdraw from the study, if they so choose.

After screening and pre-intervention assessment, participants are randomized into one of three conditions. All three conditions consist of 4 two-hour group sessions with 4 to 9 participants led by a trained facilitator. Below is a description of each condition.

**Condition 1- Traditional WORTH: WORTH (Women On the Road To Health)** is a gender-specific group-based HIV prevention intervention tailored to low income, drug-involved women in the criminal justice system that was developed by the investigative team and demonstrated to be efficacious in increasing condom use among 145 female inmates at Rikers Island, who were scheduled for release. More recently, WORTH was tested in the NIDA Clinical Trials Network and found to be effective in increasing condom use among 512 women in drug treatment. The core elements of WORTH include: HIV education, risk assessment, risk reduction problem solving, condom use skill building, negotiation skills building, partner risk assessment, relationship safety planning and IPV prevention, help-seeking and social support. The intervention will be conducted using a standardized intervention manual that was developed by the study investigative team and refined for the proposed study.

The basic format of each WORTH session remains consistent following a sequence of 5 steps: (1) an opening (grounding meditation) which provides a brief centering transition to engage participants in the work of the sessions (2) Check-in to review material from the previous session, and to discuss any incidents where participants engaged in risk behaviors and to acknowledge positive ways in which women used new skills to avoid HIV risk; (3) a discussion using case vignettes to raise awareness of links between IPV, drug-related activities, and HIV risks; (4) a skills-building component relevant to the discussion; and (5) review and update participant needs, goal development for skills-building at home, and a closing ritual. The WORTH intervention consists of four 2-hour group sessions that are led by two female facilitators. The main objectives of each session are detailed below:

Session 1: HIV information, risk, and rationalizations: (1) introduce purpose and goals of group; (2) elicit group rules, roles and obtain a commitment of confidentiality; (3) elicit reasons for wanting to take care of one’s self; (4) provide basic information about HIV disease, transmission and treatment; (5) provide basic information about STI symptoms, transmission and treatment; (6) weigh the pros and cons of HIV testing and learn how to seek testing and counseling; (7) discuss behaviors that increase health and longevity for those living with HIV; (8) make HIV and STIs more real and personal in our lives; (9) increase awareness of attitudes that put us at risk of getting HIV or STIs; (10) strengthen participants ability to challenge risk rationalizations; (11) introduction to social support network map (12) setting HIV risk reduction, social support and help-seeking goals (13) closing, homework, and WORTH affirmation.

Session 2: Managing risk: Exploring triggers, identifying behaviors, and practicing safety: (1) review last session, homework, and check-in; (2) strengthen participants’ ability to challenge personal risk rationalizations; (3) identify triggers for HIV and STI risk and make connections between triggers and risky behaviors; (4) identify supportive people in our lives as well as people who may impede our ability to stay safe and healthy; (5) Review different types of intimate partner violence (IPV) and discuss how IPV and gender role power imbalances can trigger drug use and HIV risk behaviors; (6) teach participants how to use a male condom and female condom correctly; (7) demonstrate ways to introduce safer sex that are sexy and appealing; (8) revisit progress on social support network map, help seeking and HIV risk reduction goals, (9) closing, goal setting, and WORTH affirmation.

Session 3: Problem-solving and safer sex negotiation: (1) check-in, homework review; (2) explore how self talk can create options for safe sexual behavior; (3) Introduce the POP model for problem solving, and practice using POP for a current problem; (4) Identify barriers to safer sex behavior; (5) introduction to safer sex negotiation, including risky sex refusal; (6) observe and practice skills for negotiating safer sex and refusing risky sex; (7) role play to practice putting negotiation and refusal skills into action; (8) revisit social support network map and set goals (9) injection drug use risk (10)closing, homework, and WORTH affirmation.

Session 4: Assessing risk of abuse and safety planning, managing slip situations: (1) check-in, homework review; (2) screening for IPV, providing feedback on IPV risk and making safety plans for protection; (3) reinforce recognition of IPV related triggers to unsafe sex and skills for negotiation and refusal in these situations; (4) preparing for slips to unsafe sex/drugging and cutting slips short as soon as they start; (5) making POP plans for cutting off a slip to unsafe sex; (6) developing a long-term risk reduction plan; and (7) a graduation exercise, reinforcing sense of achievement, self-worth, and community.

**Condition 2- Multimedia WORTH:** The Multimedia WORTH intervention features the same core elements as the original version, but these core elements are translated into interactive tools and culturally tailored video vignettes designed to enhance group learning and individualized feedback. Participants interact with Multimedia WORTH at two levels: (1) group materials are delivered via computer projection onto a screen and (2) participants complete individual activities and create journal logs tracking their progress on personalized goals on their personal user accounts using laptop computers. The computer multimedia support tool includes text, imagery, animations, audio and video in a format that guides the facilitator’s delivery of the intervention. There are 5 main multimedia tools used in the Multimedia WORTH program:

• Multi-sensory delivery of psycho-educational content -- Text-based in the Traditional version, the Multimedia version translates core HIV/STI transmission and prevention concepts into culturally tailored animations, videos and visual images designed to enhance learning and memory of these concepts. Culturally tailored, woman focused video testimonial segments are also incorporated to motivate participants to work though challenging issues related to reducing HIV risks and drug use.

• Skill acquisition using simulated video vignettes that provides instruction and demonstration of core skills (e.g., safer sex negotiation and problem-solving skills, technical condom use skills) using culturally congruent role models followed by simulated video vignettes of role play scenarios where participants are prompted to identify common pitfalls in using skills and to rehearse appropriate responses.

• Individual interactive exercises and logs that are designed to enhance participant’s recall of core knowledge and to track their individual progress from session to session in their own risky behaviors, current and ideal future social networks, and the types of support for sustaining safer behaviors, and future plans). Printed journals from these logs are given to participants at the end of the intervention.

• Recording mechanism captures all content and activities from the session, including interactive content for each participant, such as participant’s goals, motivations, individualized social network maps and agreed upon ground rules, as well as any other important information the participants or facilitator want to document. The computer tracks any data that the facilitator or participants enter during the sessions. This mechanism yields more precise quality assurance data on the amount of time spent on each activity and the level of participant engagement in different activities.

• Facilitator interactive guide which acts as a road map, prompting the facilitator to move sequentially through each activity without the need to rely on notes, memory or previous experience. The separate interface for facilitators uses the same computer support tool but contains a road map that guides the facilitator through the session activities and contains additional information, concepts, and models just for facilitators.

**Condition 3- Wellness Promotion:** The Wellness Promotion condition consists of general health information that is not gender-specific. SIG has used versions of this Wellness Promotion condition in previous studies such as Eban and Connect. Session content will be as follows:

Session 1: Diseases that affect women; reasons to keep ourselves healthy; prevention, detection and treatment; health risk assessment; goal setting. Session 2: Exercise assessment; benefits of exercise; physical activity for fitness; introduction to nutrition; body mass index; healthy personal eating; goal setting. Session 3: smoking and your health; alcohol; cancers and screening; getting health care; communicating with health care providers. Session 4: Attitudes about exercise; early detection and screening review; improving communication with health care providers; health basketball; graduation.

Participants are compensated $30 for each intervention session completed. Upon completion of condition 1, 2, or 3, participants complete follow-up assessments at 3-, 6-, and 12-months post-intervention. The 12-month follow-up assessment includes biological specimen testing for HIV and STI’s. All follow-up assessments are completed at the Social Intervention Group Community Research Center, and participants are compensated as follows: 3-month assessment: $35, 6­month: $50, and 12­month: $65.

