**8. Potential Risks**

Screening, assessments, and interventions should pose minimal risks to subjects participating in the study. Subjects may become embarrassed or uncomfortable while being asked questions and there is some risk that discussing sensitive topics cause distress. Because subjects take part in a group intervention, there is a risk that other group members may divulge confidential information to people outside the group. We address this by asking everyone to respect the confidentiality of the other participants. Participants are advised that conversations about HIV and safer sex negotiation may anger their male partners. This anger may put them at risk for emotional, physical and/or sexual abuse or abandonment of the relationship. Participants are advised to observe any signs of such anger in their partners and to discuss them with study staff immediately.

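### Multimedia WORTH hands women a printed journal drawn from logs of their own risk behaviours, and none of the protocol's partner-abuse or confidentiality safeguards is tied to that hand-out (minor)

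*Protocol*

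**What the plan says.** Section 3 (Study Procedures) describes the Multimedia WORTH logs as one of five multimedia tools. Among other things they are meant to "track their individual progress from session to session in their own risky behaviors, current and ideal future social networks", together with sources of support and future plans. The description ends: "Printed journals from these logs are given to participants at the end of the intervention". It attaches no question, choice, or rule on content or storage to that step.

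Section 8 (Potential Risks) tells women that "conversations about HIV and safer sex negotiation may anger their male partners" and continues: "This anger may put them at risk for emotional, physical and/or sexual abuse or abandonment of the relationship". The advice that follows is: "Participants are advised to observe any signs of such anger in their partners and to discuss them with study staff immediately". The same section then sets out crisis and referral procedures, recognises unauthorised disclosure of information shared in sessions as a risk, and says staff remind participants that they may ask for their data to be destroyed.

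The Session 4 content listed under Traditional WORTH in Section 3 includes "screening for IPV, providing feedback on IPV risk and making safety plans for protection". This applies to the multimedia arm too, because "The Multimedia WORTH intervention features the same core elements as the original version" and partner-violence prevention is listed among those core elements.

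Section 6 (Confidentiality of Study Data) and the Data Management part of Section 9 cover coding, encryption, locked storage and limits on what staff may release. Section 9 names loss of confidentiality as one of two primary risks and rates its level and probability as minimal.

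**The concern.** The protocol creates a sensitive paper document and passes it to the woman, outside the reach of its own protections. By the inclusion criteria in Section 4, every participant is under recent criminal justice supervision, reports recent unprotected sex, and reports illicit drug use or binge drinking. Each is also HIV positive or has a further HIV/STI risk, for herself or through a partner. A log of her own risk behaviours is therefore likely to hold material that could harm her if someone else read it.

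The risk section treats conversation as the trigger for partner anger. A written record can be found without the woman choosing to speak, so it is a separate route to the same harm. The protocol neither names this route nor connects any existing protection to it. What is at stake is participant safety in one arm; no estimate, error rate or test is affected.

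**Working it through.** The protocol gives no figure to reproduce on this point, so the check is a comparison of provisions.

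**Step 1. What leaves the study.** The journal is printed from logs intended "to track their individual progress from session to session in their own risky behaviors". The hand-out is stated for participants in general, at the end of the intervention. The text does not say that a woman may decline, and it does not say that she may not.

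**Step 2. Which hazards the protocol itself names.** Section 8 names partner anger leading to abuse, with conversations as the trigger. It also names unauthorised disclosure of sensitive information from screening, sessions or assessments, and breach of confidentiality about STI status, HIV status and sexual behaviour. Section 9 repeats loss of confidentiality as a primary risk. Section 8 gives other group members as one route of disclosure; it does not mention the journal.

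**Step 3. Whether each safeguard reaches the journal.**

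| Safeguard | Where | Reaches the journal? |
|---|---|---|
| Partner-violence screening, feedback and safety plans | Section 3, Session 4 | Exists for both WORTH arms; not linked to the hand-out |
| Advice to report signs of partner anger | Section 8 | General; acts after a problem has arisen |
| Crisis intervention and referral | Section 8 | General; acts after a problem has arisen |
| Destruction of data on request | Section 8 | Concerns study data; does not extend to a copy she holds |
| Coding, encryption, locked files, limits on release by staff | Sections 6 and 9 | Concern records the study holds |

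No row contains a check, choice or rule specific to the journal.

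**Step 4. Timing.** Session 4 is the last of four sessions, and journals are given out at the end of the intervention. The screening and the hand-out therefore fall close together, but nothing makes the second depend on the first.

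**Step 5. Reach.** The protocol gives 306 women, three arms and an allocation designed to balance them. With equal arms, 306 / 3 = 102 women would be in Multimedia WORTH. This is the approximate number who could be handed a journal; women absent at the end may not receive one. The protocol gives no rate of partner violence, of journals being found, or of resulting harm, so the size cannot be taken further.

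**The case against.** The strongest reply is that the protocol already takes partner violence seriously. Every WORTH woman is due for screening and safety planning in the closing session, is told to report partner anger, and has crisis referral available. Handling of the journal could also sit in the intervention manual or the policies and procedures manual, neither of which is shown. The Section 8 warning is about conversations, so the protocol does not contradict itself. All of this stands. It rules out saying that women in this arm have no safety check, and it keeps the point minor. It does not supply the missing link, and a risk section should list a disclosure route that the protocol itself creates.

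Two stronger readings are tempting.

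- **Confounding of the modality comparison.** A reader might infer that a kept journal acts as a booster over 12 months and so biases the comparison of Multimedia with Traditional WORTH. The documents do not support this. The logs and journals are a declared part of the multimedia arm, and Section 1 compares the multimedia intervention as a whole with the traditional method. The journal limits attribution to any single tool, as the other tools do, without biasing that comparison. Traditional WORTH uses pencil and paper, with homework, a social network map and a long-term plan, and the protocol does not say whether those women keep their papers. A difference in take-home material is therefore not established.
- **Exposure to supervising officers.** A reader might infer that courts or probation would seek out the journal. Section 6 reports that both have affirmed in writing that they do not seek identifiable information on participants.

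It can also be said that follow-up ended in April 2013, so the arm cannot now be changed. That is correct; the change is useful where the intervention is used again.

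**Conclusion.** The point holds as a minor participant-safety gap. The protocol gives women a printed record drawn from logs of their own risk behaviours, recognises partner abuse and disclosure as risks, and ties none of its safeguards to that record. Its confidentiality measures do not extend to a paper copy in the woman's possession.

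This rests on two assumptions: that the partner-abuse warning about conversations extends reasonably to a written record, and that the manuals not shown do not already deal with the hand-out. The reach is one arm, about 102 women if allocation was equal. The amount of harm is unknown and cannot be derived from the document. The planned statistical comparisons are unaffected.

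**What to change.** - In the Multimedia WORTH description in Section 3, have the journal offered to each woman instead of given. Before the offer, staff ask her privately whether it is safe for her to keep it, alongside the partner-violence screening and safety planning already placed in Session 4.
- State that if she declines, the study keeps the journal securely or destroys it.
- In Section 8, list the printed journal as a route of disclosure and refer to this step.

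The cost is a few sentences and one question in a session that already covers the subject; no new staff or separate procedure is needed. The downside is that some women will not keep a journal. The content of the logs and the Traditional WORTH arm need no change.
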